**Figure 3 figure3:**
[figure not shown]
Care contacts in the structured clinical care pathway from surgery until 1 year after surgery. The interdisciplinary team includes endocrinologists, neurosurgeons, nurses, dietitians, and physical therapists.

### Standard Care

All patients in the control group will receive standard care. Standard care is primarily hospital-based. In short, during the first 24 postoperative hours, the patients are monitored at a medium care unit for neurological status as well as fluid and electrolyte balance. Thereafter, monitoring for a further 5 days is conducted at the inpatient department of endocrinology. Before discharge, on postoperative day 6, evaluation of endocrine deficiencies is performed. At an outpatient visit at the department of endocrinology, 4-5 weeks postoperatively, hormonal status is rechecked, and information on any complications is collected. Thereafter, the frequency of visits to the outpatient clinic depends on tumor types, surgical outcome, hypopituitarism, and perceived symptoms.

### Strategies to Secure the Intervention Over Time

To facilitate and secure the implementation of the intervention over time, and specifically the nurse care manager’s role, the nurse assigned for quality and safety improvement at the clinic (EA) and a researcher from the research group ([name]) meet the nurse care managers regularly to support and discuss the different components of the intervention and its implementation in patient care. In addition, all staff members at the inpatient and outpatient units are informed about the study prior to starting. Specific nurses at the postsurgical endocrinology unit were identified and are involved in the performance of the study; these nurses also attend the 1-day education course. Every 3 months, the nurse assigned for quality and safety improvement at the clinic and the researcher from the research group meet with inpatient and outpatient team members including nurses, endocrinologists, neurosurgeons, research nurses, the head of nurses, and the head of physicians to provide an update on the intervention and discuss issues related to the structured clinical care pathway and other issues of relevance.

### Outcome Measures

The primary outcome measure is self-reported psychological wellbeing. Secondary outcome measures will be self-reported satisfaction of care, health status, fatigue, and self-efficacy. Additional secondary outcomes include person-centered content in documentation and patient safety.

### Participant Timeline

The patient-reported outcome measures are reported by the patients on the day before surgery and repeated at discharge from inpatient care, approximately 1 week after surgery. Two follow-ups are performed at 4-6 months and 11-13 months after surgery (Figure 4). All questionnaires for self-assessment were chosen due to their widespread use in research and good psychometric validity in both patients and healthy populations. Medical records are also reviewed.

**Figure 4 figure4:**
[figure not shown]
Schedule of enrollment, intervention and assessments for each included patient. EQ-5D-5L: Euro- Qual Five Dimensions; GSE: Generalized Self-Efficacy Scale; MFI-20: The Multidimensional Fatigue Inventory; MIDAS: The Migraine Disability Assessments; PGWB: The Psychological General Well-being instrument; QPP: Quality from the Patient Perspective Questionnaire; SNOT-22: Sino-nasal Outcome Test.

### Data Collection

#### Primary Outcome

Self-perceived psychological wellbeing is assessed with the Psychological General Well-Being scale, a 22-item questionnaire comprising 6 dimensions: anxiety, depression, positive wellbeing, self-control, general health, and vitality [28]. The Swedish version of the questionnaire has been externally validated [29]. A total score of 132 is calculated from 6-point Likert scales for each item and represents excellent psychological wellbeing.

#### Secondary Outcomes

The Euro-Qual Five Dimensions questionnaire is used to assess self-reported health status. It includes 5 specific dimensions of health: mobility, self-care, usual activities, pain/discomfort, and anxiety/depression [30-32]. The questionnaire also comprises a visual analogue scale from 0 to 100 in which the patient rates health from the worst to the best health imagined. To further explore effects on the patients’ perceived perception and intensity of fatigue, the Multidimensional Fatigue Inventory-20 is used [33,34]. Within the Multidimensional Fatigue Inventory-20, general fatigue, physical fatigue, reduced activity, reduced motivation, and mental fatigue represent the 5 dimensions of fatigue. The Generalized Self-Efficacy scale is used to measure how the patient perceives their possibility of adhering to the goals being set and find solutions to unforeseen or surprising situations and challenges [35]. As a patient-experience measure, the Quality from the Patient's Perspective questionnaire is used [36,37]. Patients rate their experience and subjective importance in aspects of care: medical-technical competence, identity-oriented approach, sociocultural atmosphere, and physical-technical conditions. Documentation held by both health care professionals (eg, medical records) and patients (eg, the health book) are reviewed with respect to person-centered content [38]. Aspects of patient safety are reviewed from medical records (eg, the assessment of symptoms and vital signs) and care planning as well as specific aspects of care following surgery and introduction of hormonal replacement therapy.

### Retention and Data Management

The research nurse is responsible to schedule follow-up visits in the longitudinal assessment. The research nurse ensures that the scheduled appointments are kept and that data are collected. Reasons for missing data or discontinuation from the study are documented. Updated information on recruitment and follow-up are continuously discussed within the research group to identify structural barriers for inclusion or data collection. A file for data collection on the patients including their social security number and assigned code number is kept in a locked safe at the clinic. Self-reported measures are primarily collected through electronic devices. Data are entered with the code number assigned to each patient. Clinical data such as diagnosis, surgery, medical treatment, radiotherapy, mortality, morbidity, care contacts, and hospitalization are collected from the patients' medical records and entered into data files. Researchers within the research group are responsible for monitoring data collection.

### Plan for Statistical Analysis

Statistical analysis will include descriptive analysis and comparisons between the control and intervention groups. For numerical data, mean, SD, median, and interquartile range will be calculated. Categorical data will be expressed as proportions (%). Background and clinical characteristics for the two groups will be expressed with descriptive data, and differences will be analyzed with the chi‐squared test, independent samples *t* test, or Mann-Whitney U test. The primary outcome will primarily be evaluated by comparing changes in psychological wellbeing between baseline and 1 year after surgery in the two groups. Parametric or nonparametric tests will be used depending on whether data are normally distributed for the purpose of comparing data between the intervention group and control group. Effects will be described as mean differences with 95% CIs. Data will be analyzed using SPSS software package (IBM Inc, Armonk, NY). The significance level will be set at *P*<.05, and all tests will be two-tailed. Subgroup analyses will be performed based on demographic characteristics and disease and treatment characteristics.

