### Study Population

All consecutive patients diagnosed with a pituitary tumor planned for neurosurgery at the study center will be asked to participate in the study. Inclusion criteria are planned neurosurgery and ≥18 years of age. Exclusion criteria comprise health conditions that might restrict understanding of the study or ability to adhere to the protocol (eg, cognitive impairments or drug addiction). The power calculation for estimation of sample size was based on two previous hormonal replacement therapy interventions evaluating improvement in psychological general wellbeing [26,27]. We used a range of d values due to different study designs; based on d=0.3326 (no treatment vs treatment in a crossover design) [27] to d=2.826 (before and after intervention) [26], 64-100 patients are needed in each group to obtain an 80% power with a 95% significance. Considering the different design of the study, 90 patients are targeted in each group, also taking into account a 10% discontinuation rate.

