### Recruitment

Recruitment is coordinated by a research nurse ([name]) experienced in the care of patients with pituitary tumors and specifically trained in endocrine research studies. Patients who are planned for surgery and are eligible for the study will be contacted by phone about 1 week before surgery to receive information regarding the study. A written description of the study is sent to the patients after this initial contact. The same nurse meets the patient on the day before surgery to inform about the study again. After answering any potential questions regarding the study, patients provide written informed consent. In the case of acute surgery, the neurosurgeon responsible for the patient obtains verbal and written consent before surgery. No study activities are initiated before verbal and written informed consent.

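### The primary test on the two-point PGWB change makes no use of the 4-6-month score and is open to a modest bias if loss differs between the sequential groups; a repeated-measures model of the same contrast would be more robust

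*Protocol article*

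**What the plan says.** Protocol article, Plan for Statistical Analysis: the main evaluation of the primary outcome is made by "comparing changes in psychological wellbeing between baseline and 1 year after surgery" in the two groups. On the method: "Parametric or nonparametric tests will be used depending on whether data are normally distributed". On the effect measure: "Effects will be described as mean differences with 95% CIs". No longitudinal model is named for the primary comparison.

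Participant Timeline: patient-reported measures are completed the day before surgery and at discharge, about a week after it. After that, "Two follow-ups are performed at 4-6 months and 11-13 months after surgery". The schedule figure is not shown, so it is an inference from this general statement that the Psychological General Well-Being scale (PGWB) is among the measures at 4-6 months. It is a very likely one.

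Study Population: the target of 90 per group is set "also taking into account a 10% discontinuation rate".

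Retention and Data Management: a research nurse schedules the follow-up visits and sees that they are kept, and reasons for missing data or discontinuation are recorded. The article gives no analysis set, imputation rule or complete-case rule.

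**The concern.** A two-group test on a change score needs both ends of the change. A patient seen at baseline and at 4-6 months but not at 11-13 months contributes nothing unless the last value is filled in, although the mid-year score says something about where that patient was heading. Enrolling more patients to cover the expected loss restores the number of completers. It does not make the completers representative.

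This matters more here than in a randomised trial with equal follow-up. Under Study Design the groups are recruited one after the other and are described as nonequivalent. Under Intervention each intervention patient has an allocated nurse care manager and a structured contact plan for a year. Under Standard Care, the controls' clinic visits after the 4-5-week check depend on tumour type, surgical result, hypopituitarism and symptoms. Loss that is related to wellbeing and unequal between groups is therefore plausible, though not shown. It would move the estimated group difference in change in a direction that cannot be known in advance.

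**Working it through.** **1. The plan's own allowance.** Inputs from Study Population: 90 per group, 10% discontinuation. 90 × (1 − 0.10) = 81 completers, and 81 / (1 − 0.10) = 90. The loss is consistently budgeted.

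**2. What the allowance protects.** Two-sided 5% (Plan for Statistical Analysis), 80% power (Study Population), normal approximation: detectable d = (1.96 + 0.84) × √(2/n).

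- n = 90: d = 0.418
- n = 81: d = 0.440

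The loss costs little precision. The 0.44 is derived here from 81 completers; the article does not state it. The article's range of 64-100 per group corresponds to d of about 0.5 to 0.4 and does not follow from the d values printed beside it. That is a separate matter and is not used here.

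**3. Possible bias of a completers-only change comparison.** The article gives no dropout rate by group and no correlations, so these are assumptions:

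- PGWB scaled to SD 1 at each visit, with no true group effect.
- Loss before 1 year depends on the 4-6-month score (lower scores leave more often; logistic, log-odds slope −1 per SD).
- Set A, correlations baseline-mid 0.5, baseline-1 year 0.4, mid-1 year 0.7. Set B: 0.4, 0.3, 0.8.

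If completers' mean mid-year score is shifted by s, their mean change is shifted by (r[mid, 1 year] − r[baseline, mid]) × s. Integrating the logistic model over a standard normal score gives s = 0.133 for 15% loss and s = 0.047 for 5% loss. With 15% in controls and 5% in the intervention group, the shift in intervention minus control is:

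- Set A: (0.7 − 0.5) × (0.047 − 0.133) = −0.017 SD
- Set B: (0.8 − 0.4) × (0.047 − 0.133) = −0.034 SD

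Large-sample simulation agrees (intervention minus control, SD of the PGWB score):

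| Loss, control / intervention | Set A | Set B |
|---|---|---|
| 10% / 10%, same mechanism | 0.003 | −0.001 |
| 10% / 10%, score-related in controls only | −0.019 | −0.035 |
| 15% / 5% | −0.019 | −0.035 |
| 20% / 10% | −0.016 | −0.033 |
| 5% / 15% | 0.019 | 0.034 |
| 10% / 10%, opposite mechanisms (extreme) | −0.038 | −0.076 |

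An estimator that predicts the missing 1-year score from baseline and the mid-year score left no more than 0.003 SD in every row. If all visit correlations are equal (0.5 or 0.7), the multiplier in the formula is zero, and simulated bias was within 0.007 SD for every pattern.

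**4. Size in context.** 0.019 / 0.44 = 4% and 0.035 / 0.44 = 8%. The 0.44 is in SDs of the analysed variable. If that is the change, its SD is √(2(1 − r[baseline, 1 year])): 1.10 in set A and 1.18 in set B. The bias is then 0.017 and 0.030, or about 4% and 7% of 0.44.

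**The case against.** The strongest objection is that the article never says patients with a missing score are excluded. A reader might infer that the primary analysis is complete-case and drops everyone lacking either value. The documents do not support that. They name a contrast and a family of tests, a change can be computed after imputation, and missing-data rules are commonly left to a full protocol or SAP that is not shown. That silence is no finding, and the point does not rest on it. What remains is a stated choice: a two-point test that by itself cannot use a partly observed patient and has no place for the mid-year score. The text says the outcome is primarily evaluated this way, which leaves room for supporting analyses but keeps the two-point test as the main one.

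Differential dropout is also not shown to be likely. The research nurse's scheduling duty is not limited to one group, and controls do have clinic visits. This lowers the risk without showing equal retention.

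A reader might also infer missing baselines from the acute route: "In the case of acute surgery, the neurosurgeon responsible for the patient obtains verbal and written consent before surgery". Nothing there says the PGWB is not collected, the number of such cases is not given, and the inclusion criterion is planned surgery. That is conjecture.

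A larger bias is tempting too. If leavers are 0.5 SD worse at 1 year, 0.15 × 0.5 − 0.05 × 0.5 = 0.05 SD, about 11% of 0.44. But that deficit is in level, and the outcome is change. If the deficit carries back to baseline with correlation 0.5 (assumed), the gap in change is 0.5 × (1 − 0.5) = 0.25 and the shift is 0.10 × 0.25 = 0.025 SD. If leavers are equally worse at both visits, it is zero.

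Finally, a change comparison fits the pretest-posttest design, and using fewer visits than were collected is not an error. Both are true, which is why the fix keeps the change contrast and alters only how it is estimated.

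**Conclusion.** The point stands as a cheap improvement to the primary analysis, not as an error that invalidates it. The two-point test leaves collected information unused, and the 10% allowance covers precision only. With unequal loss (15% against 5%, or 20% against 10%), or loss related to wellbeing in the control group only, bias is about 0.02 to 0.035 SD in either direction, against a detectable 0.44 SD. It is 0.04 to 0.08 SD in a deliberately extreme case, and near zero if loss is alike in both groups or the visit correlations are equal. All of this rests on assumed dropout rates, correlations and a dropout mechanism that depends on the mid-year score, and on PGWB being collected at 4-6 months.

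**What to change.** Make the primary analysis a likelihood-based repeated-measures model with PGWB at baseline, 4-6 months and 11-13 months all as responses. Include group, visit and group-by-visit terms and an unstructured covariance, and leave the baseline means unconstrained, because the groups are not randomised. The primary estimate is the group difference in change from baseline to 11-13 months, with its 95% CI.

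This keeps the planned estimand: with complete data the estimate equals the simple difference in mean changes. Entering baseline PGWB as a covariate would not keep it, because in nonequivalent groups that targets a different quantity. Patients with a missing visit stay in under missing-at-random given their observed scores, which is weaker than what a completers-only comparison needs but is still an assumption. Report the two-point change test as a sensitivity analysis.

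The cost is a few lines of plan wording and slightly more modelling, in the SPSS package already named. No new data are needed.

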## Methods

### Study Design

The study utilizes a quasiexperimental design with a nonequivalent control group and a pretest-posttest study design. The study is carried out in two sequential steps: (1) a control group of patients receiving standard care up to 1 year after surgery followed by (2) an interventional group where patients receive extended support within a person-centered practice up to 1 year after surgery.

The study is conducted according to the Declaration of Helsinki. All participants in the study have rights to confidentiality and provide written informed consent [25]. Approval for the protocol has been obtained from the regional ethical review board (approval reference 387-15). Any modifications to study procedures have to be reported as formal amendments to the ethical review board for approval.

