### Intervention

The structure and content of the intervention are built on principles for person-centeredness. Within the intervention, repeated patient narratives and continuously revised, documented health care planning ensure that the care is systematically practiced according to principles for person-centeredness (Figure 2). Self-management support*,* being an important component in the intervention, is primarily conducted between the patient and a nurse care manager. Each patient in the intervention is allocated a hospital-initiated nurse care manager, who initiates the first contact with the patient at the inpatient unit before discharge after surgery. The primary goal of the support from the nurse care manager is to facilitate the patient’s own resources in managing illness as well as giving specific health education on, for example, physical activity and diet. Patient-held documentation, the health book, frames the content of self-management support. The health book includes detailed information on the structured clinical care pathway, contact information for the nurse care manager, and preparatory questions that could be used before appointments with the health care team. Questions to encourage reflections on good and bad days and what constitutes or hinders good health are also included in the health book. After each contact between the patient and nurse care manager, a health plan, including agreed goals, is revised. Within the health book, it is also possible for the patient to self-assess and monitor symptoms and health in writing or by drawing. They are also able to reflect and self-assess issues related to work, social support, economy, and other health factors such as physical activity, sleep, sex life, and diet.

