## Results

Inclusion in the control group receiving standard care was completed from Q3 2015 to Q4 2017 with the number of patients needed to evaluate the primary outcome. Recruitment to the group exposed to the intervention has been ongoing since Q4 2017, and the estimated timepoint for completed recruitment is Q4 2020. Final data collection is expected in Q4 2021.

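### The primary change score spans the operation but support begins only after it, so a difference between the two recruitment periods in surgical result or early hormone loss is counted as support effect

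*Protocol article*

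**What the plan says.** All references are to the protocol article.

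- **Design.** Study Design describes a "quasiexperimental design with a nonequivalent control group and a pretest-posttest study design" and adds that "The study is carried out in two sequential steps", controls first. Results dates the periods: "Inclusion in the control group receiving standard care was completed from Q3 2015 to Q4 2017", with intervention recruitment running from Q4 2017 to an expected Q4 2020.
- **Measurement.** Participant Timeline states that the patient-reported outcomes are "reported by the patients on the day before surgery and repeated at discharge from inpatient care, approximately 1 week after surgery". It continues: "Two follow-ups are performed at 4-6 months and 11-13 months after surgery".
- **Start of support.** Under Intervention, each patient is given a nurse care manager "who initiates the first contact with the patient at the inpatient unit before discharge after surgery".
- **Early endocrine status.** Standard Care says: "Before discharge, on postoperative day 6, evaluation of endocrine deficiencies is performed". Hormones are checked again at the outpatient visit 4-5 weeks after surgery.
- **Primary analysis.** Plan for Statistical Analysis says the primary outcome is mainly evaluated by "comparing changes in psychological wellbeing between baseline and 1 year after surgery in the two groups", with a parametric or nonparametric two-group test and a mean difference with 95% CI. It names no adjustment. Clinical characteristics are described and tested between groups, and subgroup analyses by disease and treatment characteristics are planned.

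**The concern.** The window over which the effect is measured opens before the window of exposure. The score starts the day before surgery, whereas support starts some days after it. What the operation achieved, its complications and early loss of pituitary function all fall between the two.

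In a randomized trial this would add noise only. Here the groups were operated on in different periods, so a difference between periods in any of these events moves the primary estimate and cannot be separated from an effect of support. Such events arise after the baseline questionnaire. Subtracting baseline PGWB does not remove them, and adjusting for preoperative characteristics removes only the part those characteristics predict. The article judges randomization impossible (Discussion), so protection against this bias has to come from the analysis.

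**Working it through.** **1. Order of events, from the sections cited above**

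| Time | Event | In primary change? | Support begun? |
|---|---|---|---|
| Day before surgery | Baseline PGWB | start | no |
| Surgery and first ward days | Operation, complications, early hormone loss | yes | no |
| On the ward, day not stated | First nurse care manager contact | yes | begins |
| Postoperative day 6 | Endocrine evaluation | yes | order against contact not stated |
| Discharge, about 1 week | Questionnaires repeated | yes | order against contact not stated |
| 4-5 weeks | Hormones rechecked | yes | yes |
| 11-13 months | Final PGWB | end | yes |

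**2. The plan's own figures.** The article gives no expected period difference, so there is no figure of its own to reproduce for the bias. The yardstick is the effect the trial can detect. Study Population targets 90 per group with 10% discontinuation: 90 × 0.90 = 81 evaluable. At two-sided 5% and 80% power,

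d = (1.96 + 0.84) × √(2/81) = 0.44.

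The 64-100 per group printed in that section does not follow from its printed effect sizes: d=0.3326 gives 142 per group in a two-sample comparison, and d=2.826 gives about 2 to 4. That is a separate matter, and nothing below depends on it.

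**3. Size of the bias (assumed inputs).** Bias in SD = difference between periods in the proportion with a deficit × effect of that deficit on PGWB.

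- 0.10 × 0.5 SD = 0.05 SD; 0.05/0.44 = 11% of the detectable effect.
- 0.20 × 0.5 SD = 0.10 SD; 0.10/0.44 = 23%.

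Both the 10-20 points and the 0.5 SD are assumptions.

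**4. Effect on the test.** With no true support effect and a bias of b SD of the change score, SE = √(2/81) = 0.157 and

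rejection rate = Φ(b/SE − 1.96) + Φ(−b/SE − 1.96).

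| b (SD) | 81 per group | 90 per group |
|---|---|---|
| 0 | 5.0% | 5.0% |
| 0.05 | 6.2% | 6.3% |
| 0.10 | 9.8% | 10.3% |
| 0.20 | 24.7% | 26.9% |

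The 0.20 row would need, for example, 20 points × 1.0 SD. A bias in the other direction would hide a real effect instead.

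**5. What the discharge reading can show.** With 90 per group, the 95% CI for the group difference in baseline-to-discharge change has half-width 1.96 × √(2/90) = 0.29 SD. That is about three to six times the biases in step 3.

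**The case against.** The strongest reply is that the article contains no error here. The preoperative PGWB is the only value certain to be free of support, which makes it the natural baseline. The nonequivalent sequential design is declared and justified. Surgical and clinical data are collected (Retention and Data Management), group differences are tested and subgroups are planned. The documents describe no change in surgery between periods. Tumor type and growth pattern, which the article says strongly influence remission, precede surgery, so part of the problem is ordinary case mix.

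Most of this stands. The baseline should stay, and the size of the bias is unknown. But describing imbalance and running subgroups does not correct the primary estimate, and declaring the design does not either.

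A reader might infer several stronger points that the documents do not support:

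- *That the discharge PGWB is ignored.* The article gives it no stated role, but it describes only the main evaluation and condenses a fuller plan. The figure listing instruments by visit is not shown.
- *That the discharge PGWB would expose the bias.* At about 1 week it reflects acute recovery. Hormone status is rechecked at 4-5 weeks, and tumor control shows later still. Step 5 shows that its precision is too low for the biases assumed.
- *That it is a clean pre-support reading.* First contact precedes discharge and the questionnaire is completed at discharge, so contact may well come first. Ward nurses trained for the study also work on that unit.
- *That the sino-nasal score at 1 year could serve as a negative control.* The visible text does not show that it is collected then, and support that covers symptoms might affect it.
- *That the larger sample-size effect, d about 2.8, measures the possible bias.* It is a before-after effect of hormone replacement, not a difference between patients at 1 year in a setting where deficits are evaluated and treated.

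**Conclusion.** The concern holds as a weakness of the stated primary comparison. The unadjusted change score counts as support effect any difference between periods in surgical result, complications or early hormone loss, and the sign could be either way. Under the assumption of 10-20 points and 0.5 SD, the bias is 0.05-0.10 SD, which is 11-23% of the detectable d=0.44, and the two-sided false-positive rate is about 6-10% instead of 5%. These figures illustrate sensitivity; they are not evidence that the periods differ. The point does not show that the preoperative baseline is wrong, nor that the result will be uninterpretable. It shows that an inexpensive adjustment, available from data in hand, is absent from the analysis as stated.

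**What to change.** 1. **Adjusted analysis.** Pre-specify, beside the unadjusted result, a regression of 1-year PGWB on group, baseline PGWB, tumor type, and the surgical and endocrine facts established by about postoperative day 6 (complications, new deficiency). These are fixed before support can plausibly act, so adjusting for them does not remove a support effect. Leave out hormone status or treatment from later visits, which fall within the support period. The day 6 evaluation is described under Standard Care; this proposal assumes that the intervention group has it too.
2. **Order of events.** For patients still to be enrolled, have the discharge questionnaire completed before the first nurse care manager contact where feasible. Record the order for all intervention patients.
3. **Warning signal.** Report the group difference in baseline-to-discharge PGWB change with its 95% CI (half-width about 0.29 SD). It can flag a large period difference. State in advance that a null result is no reassurance.

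**Cost.** A little more analysis of data already collected and one ward instruction. The drawback is that discharge readings in the intervention group will differ in order between earlier and later patients, which is why the order must be recorded. Adjustment reduces the bias only as far as the recorded facts capture the difference between periods.

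### The primary test may switch to ranks while the effect stays a mean difference, so the P value and the 95% CI for PGWB change can address different quantities

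*Protocol article*

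**What the plan says.** The Plan for Statistical Analysis defines the primary comparison: "The primary outcome will primarily be evaluated by comparing changes in psychological wellbeing between baseline and 1 year after surgery in the two groups". The next sentence sets how the test is chosen: "Parametric or nonparametric tests will be used depending on whether data are normally distributed". The one after sets how the effect is reported: "Effects will be described as mean differences with 95% CIs". No other effect measure is given for the case in which a nonparametric test is used. On the decision threshold, the section reads "The significance level will be set at" P<.05, "and all tests will be two-tailed".

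The section names specific tests only for background and clinical characteristics, where it lists the chi-squared test and "independent samples *t* test, or Mann-Whitney U test". Mann-Whitney is therefore the likely nonparametric test for the primary outcome, but this is an inference.

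**The concern.** In the parametric branch the P value and the interval belong together: a t test gives P<.05 exactly when its own 95% CI excludes zero. In the nonparametric branch that link is lost. A rank test responds to whether patients in one group tend to score higher than those in the other. The CI describes the difference in means. With skewed data the two can lead to different conclusions.

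The trial could then report P<.05 beside a CI for the mean difference that includes zero, or the reverse, on its main hypothesis. The design makes this more than theoretical. Study Design describes sequential, nonequivalent groups, so randomization does not ensure that the two groups have the same distribution of change when the support has no effect.

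**Working it through.** **Inputs from the protocol**
- Evaluable patients: 90 targeted per group with 10% discontinuation (Study Population). 90 × (1 − 0.10) = 81 per group; in reverse, 81 / 0.90 = 90.
- Two-sided 5% level and the reporting rule: Plan for Statistical Analysis.
- The power paragraph gives standardized effect sizes only. It supplies neither an SD nor a shape for PGWB change.

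**Assumptions**
- Switching rule: Shapiro-Wilk at 5% in each group. If either rejects, Mann-Whitney is used; otherwise the t test.
- Distributions: normal, t with 5 degrees of freedom (t5), or gamma with shape k, centred and scaled as s × (G − k)/√k, which has mean 0 and SD s. Smaller k means more skew.
- True means are equal in every scenario.

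**Step 1: what each statistic addresses.** Mann-Whitney tests identical distributions, through P(X<Y) + ½P(X=Y) compared with ½. The Welch interval is the difference in means ± t × √(s₁²/n₁ + s₂²/n₂). Under a pure shift they agree in direction. With skewed groups that differ in shape or spread, the means can be equal while P(X<Y) differs from ½.

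**Step 2: simulation, 81 per group, 10,000 trials per scenario.** Monte Carlo error at 5% is 1.96 × √(0.05 × 0.95 / 10,000) = 0.0043, about 0.4 points. Entries are percentages of trials. The last column counts trials in which the switched test and the t test (taken to match the CI) differ on significance.

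| Scenario, equal means | Rank branch used | Welch rejects | Mann-Whitney always | Switching rule | Disagree |
|---|---|---|---|---|---|
| Both normal, same | 9.7 | 5.2 | 5.1 | 5.3 | 0.4 |
| Both t5, same | 74.4 | 5.5 | 5.5 | 5.6 | 2.9 |
| Both gamma 2, same | 100 | 4.9 | 4.8 | 4.8 | 3.4 |
| Both gamma 4, same | 99.0 | 4.5 | 5.0 | 5.0 | 2.8 |
| Normal, SD 1 v 1.5 | 9.7 | 5.1 | 5.2 | 5.3 | 0.4 |
| Gamma 4, SD 1 v 1.25 | 99.0 | 5.5 | 6.6 | 6.6 | 4.5 |
| Gamma 4, SD 1 v 1.5 | 99.0 | 5.3 | 10.1 | 10.2 | 8.2 |
| Normal v gamma 4, same SD | 90.6 | 4.7 | 7.1 | 7.2 | 5.3 |
| Gamma 4 v its mirror image | 99.1 | 5.0 | 17.6 | 17.6 | 15.9 |

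The mirror-image row is a deliberate extreme.

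**Step 3: a second set with assumed SDs of 18 and 24.** The first three result columns use 6,000 trials per scenario. The last column is a separate run of 5,000.

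| Scenario, equal means | Switching rule | Welch | Disagree | Switching rule / Mann-Whitney always |
|---|---|---|---|---|
| Normal v gamma 2, SD 18 | 9.5 | 4.9 | 7.9 | 9.6 / 9.6 |
| Normal v gamma 4, SD 18 | 8.5 | 5.2 | 5.8 | 8.1 / 8.0 |
| Normal v gamma 8, SD 18 | 5.8 | 4.8 | 3.3 | not run |
| Gamma 2, SD 18 v 24 | 11.4 | 5.2 | 10.2 | 11.3 / 11.3 |
| Gamma 4, SD 18 v 24 | 7.7 | 4.7 | 6.4 | 7.5 / 7.5 |

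With identical skewed groups the switching rule rejected in 4.9%. With normal data and SD 18 v 24 it rejected in 5.3%, with 0.3% disagreement.

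**Step 4: where the excess comes from.** In both tables the switching rule and a Mann-Whitney test fixed in advance reject almost equally often. In the first table the largest gap is about 0.2 points (5.29% v 5.05%, both groups normal). The look at normality adds essentially nothing. The excess arises when a rank test is read as a test of equal means.

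**The case against.** A reader might infer that choosing the test from the data breaks the 5% level. The protocol does not support that. When both groups share one distribution, the switching rule rejects in 4.8-5.6% of trials, and elsewhere it matches a rank test fixed in advance. A rank test that rejects because the distributions differ is not in error under its own null hypothesis.

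A reader might also argue that unequal shapes at equal means are to be expected because support helps some patients more than others. If it helps some and harms none, the means differ and rejection is correct. The equal-means scenarios rest instead on nonequivalent groups differing for other reasons. That is possible under this design but not established, and the SDs and shapes are assumptions. With normal data there is practically no effect.

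It is also fair to say that the plan implies a decision rule: significance is set for the tests, and effects are only described by mean differences, so the P value decides. The normality criterion and the name of the primary test are details that a condensed article may leave to an analysis plan, and their absence is not criticized here.

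What remains is the stated pairing. Even if the P value decides, the published interval in the rank branch does not describe what was tested, and it may point the other way.

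**Conclusion.** The point holds as a mismatch between test and estimate on the primary outcome, and it follows from the text alone. Its size depends on assumptions: 81 per group, a Shapiro-Wilk switch, Mann-Whitney as the rank test, and the distributions chosen.

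Under those assumptions the switched test and the mean-based test disagree on significance in about 3% of trials when the groups share one skewed or heavy-tailed distribution. They disagree in about 3-10% when means are equal but skewed groups differ in shape or spread. In the latter case rejection is about 6-11%, against about 5% for Welch; the mirror-image extreme gives 17.6%.

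The sound conclusion is that the 5% level is not guaranteed for the mean difference that is reported. It would be wrong to say that the level is generally lost. The change should be made, but the trial's validity does not turn on it.

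**What to change.** For the primary outcome, replace the normality-dependent choice with one mean-based analysis used whatever the distribution. Either Welch's t test on PGWB change from baseline to 1 year, or a baseline-adjusted mean difference with a robust or bootstrap CI, would serve. Take the P value and the 95% CI from that same analysis, and keep Mann-Whitney as a labelled sensitivity analysis.

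Possible wording: *The primary analysis compares mean change in PGWB total score from baseline to 1 year between groups by Welch's t test. The mean difference, its 95% CI and the P value are taken from this analysis regardless of distribution. A Mann-Whitney test is a sensitivity analysis and does not decide the primary hypothesis.*

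Secondary outcomes need not all follow this rule. Where a rank test is kept, report its matching estimate and CI, such as the Hodges-Lehmann shift.

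The cost is plan wording, with no added patients, visits or measurements; the analysis can be run in SPSS, which the plan already names. The possible downside is a small loss of efficiency if the data are strongly skewed or heavy-tailed. Protection against non-normality is not a reason to keep the switch: at 81 per group Welch's test stayed between 4.5% and 5.5% in every scenario above. The choice should be fixed before the groups' 1-year data are compared.
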